12.6.5 Response to the Opinion of the Accredited Clinical Research Review Committee

When the committee gives its opinion, the principal investigator shall report to the administrator of the medical institution on the opinion given by the committee. If specific action is required based on the opinions expressed by the committee, the principal investigator shall report to the administrator of the medical institution, including the details of that action.

The Principal Investigator shall provide information to the other Principal Investigators to that effect, and the other Principal Investigators shall promptly report the contents of the information provided to the administrator of the medical institution.

12.6.6 Bug Reporting

Not applicable.

# **13. Discontinuation criteria and procedures**

## 13.1 Discontinuation criteria

If any of the following criteria are met, the subject's participation in the study will be discontinued

1. If the subject requests to withdraw consent
2. If, after provisional registration, it is found that the applicant does not meet the selection criteria or violates the exclusion criteria and is inappropriate as a target
3. If it is found after this registration that the criteria for starting dosing are not met
4. When it is difficult to continue the research due to worsening of symptoms or findings of the diseases, etc.
5. When it is difficult to continue the research due to the occurrence of adverse events
6. In the event of a serious deviation from the research protocol
7. death
8. If you find out you are pregnant
9. When the principal investigator or sub-investigator judges that the continuation of the research is not desirable.

## 13.2 Discontinuation Procedure

If a subject is found to meet the discontinuation criteria, the principal investigator or sub-investigator will explain this to the subject, discontinue the study, and take appropriate measures. If the subject is judged to be ineligible at the time of provisional enrollment, the preparation of a case report is not required, and the study will be terminated without discontinuation. If a subject requests discontinuation of the study, appropriate efforts will be made to ascertain the reason for the discontinuation with full respect for the subject's rights.

1. Discontinuation procedure before taking study medication

If the research is discontinued without taking the research medication, the principal investigator or sub-investigator should enter the date of discontinuation (the date when the decision to discontinue was made) and the reason for discontinuation in the case report form.

1. Discontinuation procedure after taking study medication

Except in cases where the subject's cooperation is not obtained, the investigator will investigate the status of the subjects taking the study drug (if during the administration period) and the occurrence of diseases, etc., as well as the tests and evaluations prescribed for discontinuation. The principal investigator or sub-investigator will enter the date of discontinuation (the date when the decision to discontinue is made) and the reason for discontinuation in the case report form.

The principal investigator or sub-investigator will confirm the presence or absence of diseases, etc., and if diseases, etc., is detected, follow-up investigations will be conducted in principle.

## 13.3 Post-treatment after completion (discontinuation) of protocol treatment

Not applicable.

# **14. Discontinuation of the study**

　　If any of the following situations occurs and the Principal Investigator, the Accredited Clinical Research Review Committee, or the administrator of the implementing medical institution judges that the study should be discontinued, the entire study may be discontinued.

In case of unpredictable serious diseases, etc., which may be detrimental to the whole subject.

Serious violations of or non-compliance with the Act and related laws and regulations or the research protocol are found.

In the event that facts are obtained that undermine or may undermine the ethical validity or scientific rationality

If a significant risk to subjects is identified.

In the event that an opinion is expressed to the Authorized Clinical Research Review Committee

In the event that the Minister of Health, Labor and Welfare requests or recommends that the Company cease operations.

In the case of discontinuation, the principal investigator will report to the principal investigators of all the institutions, the accredited clinical research review committee, and the administrators of the institutions. In addition, he or she will contact the subjects and inform them of the change in the research schedule. In addition, the subject will be promptly informed of the change and the next visit will be arranged to confirm the safety of the subject.

In addition, within 10 days of the date of discontinuation, the Principal Investigator shall prepare a Uniform Form 11 Notice of Discontinuation and notify the Accredited Clinical Research Review Committee. The principal investigator shall prepare Form 4, "Notification of Discontinuation of Specified Clinical Research," and submit it to the Minister of Health, Labor and Welfare. Even when the research is discontinued, the primary endpoint report, the summary report, and the summary report shall be prepared appropriately, and periodic reports and disease reports shall be conducted until the preparation of these reports and the completion of the research.

# **15. Effectiveness and Safety Evaluation Committee**

An efficacy and safety evaluation committee will not be established in this study.

# **16. Statistical analysis**

16.1 Target population for analysis

We define the following three analysis populations.

16.1.1. full analysis set (FAS)

The population shall consist of all enrolled subjects, excluding subjects who fall into any of the following categories.

Subjects with serious violations of selection and exclusion criteria

Subjects who have never received protocol treatment.

Subjects for whom no data other than those collected at the time of enrollment in the study have been collected since enrollment.

16.1.2. target population conforming to the research protocol (per protocol set: PPS)

The population of FAS shall exclude subjects who fall into the following categories

1. Subjects missing the primary endpoint
2. Subjects with problems such as use of contraindicated drugs, low dose compliance, untraceable and missing values, etc.*

*The details of the criteria for acceptance or rejection will be developed after the start of the examination when the acceptance or rejection will be considered.

16.1.3. safety analysis set (SAS)

The population will consist of all subjects who have received at least one dose of the study drug.

16.2 Basis for setting the target number of cases

The target number of patients is 40 cases for this registration.

[Basis for setting]

　　There are no studies investigating the recovery of defecation desire by treating chronic constipation. According to a WEB survey [4] of 2098 Japanese patients conducted at Yokohama City University, the rate of loss of defecation desire (no defecation desire: none + almost none) before treatment for Rome IV chronic constipation and in healthy adults was 57.4% (no defecation desire: none + almost none). 1484/2587 cases) and 8.3% (214/2587 cases), and the rate of defecation desire disappearance in outpatient treatment cases was 27.1% (120/443 cases).

Since the subjects of this study were "patients without defecation desire " who had already been treated for chronic constipation within the scope of usual care, the expected improvement rate of loss of defecation desire was assumed to be 45%, which was lower than 62.1%. The threshold rate of spontaneous change in defecation desire was assumed to be 20%. If the threshold is 20%, the expected value is 45%, the one-sided α is 0.025, and the total number of cases is 37, the power is calculated to be 91.6%, which is statistically significant if the number of cases is 13 or more out of 37. Although within the scope of normal practice, we considered that some patients may drop out of the study after provisional enrollment, so we judged that 40 cases was an appropriate target number of patients for this study.

The number of patients with chronic constipation who were expected to meet the eligibility criteria, including "no defecation desire," at each institution was examined, and it was determined that the number of patients could be accumulated without problems within the study period (the planned enrollment period of approximately six months).

16.3.2 Analysis of secondary endpoints (efficacy)

　　Analysis of secondary endpoints will be performed for FAS.

The significance level of the test is set at 5% two-sided.

The details of the analysis should be described in the statistical analysis plan.

(1) Changes in the following items in each week of the treatment period and comparison of the fourth week of the treatment period with the second week of the observation period

1. Presence of defecation desire: patient questionnaire

Summary statistics of the presence or absence of defecation desire at each week of the treatment period will be calculated and compared with the second week of the observation period by the Wilcoxon signed rank test for the fourth week of the treatment period.

2. Satisfaction with defecation desire: patient questionnaire

Summary statistics of satisfaction with defecation desire at each week of the treatment period will be calculated and compared with the second week of the observation period by the Wilcoxon signed rank test for the fourth week of the treatment period.

3. Satisfaction of straining: patient questionnaire

Summary statistics will be calculated for the level of satisfaction with pushing/bearing down at each week of the treatment period, and the results will be compared with those of the second week of the observation period using the Wilcoxon signed rank test for the fourth week of the treatment period.

4. Degree of straining: patient diary

In the fourth week of the treatment period, the frequency and rate of the degree of straining will be calculated and compared with the second week of the observation period by the Wilcoxon signed rank test.

5. Presence of a sense of incomplete evacuation: patient diary

The frequency and percentage of the presence or absence of a sense of incomplete evacuation at each week of the treatment period will be calculated and compared with the second week of the observation period by the McNemar test for the fourth week of the treatment period.

6. Satisfaction with treatment: patient questionnaire

Summary statistics will be calculated for treatment satisfaction at each week of the treatment period, and the results will be compared with those of the second week of the observation period using the Wilcoxon signed rank test for the fourth week of the treatment period.

7. Spontaneous bowel movement (SBM) frequency

Summary statistics will be obtained for the number of SBMs during the 7-day period (total number of SBMs during the 7-day period) at each week of the treatment period, and the corresponding t-test will be performed for the change in the number of SBMs during Week 4 of the treatment period from Week 2 of the observation period.

8. Complete spontaneous bowel movement (CSBM) frequency

Summary statistics will be obtained for the number of CSBMs during the 7-day period (total number of CSBMs during the 7-day period), and corresponding t-tests will be performed for the change in the number of CSBMs during Week 4 of the treatment period from Week 2 of the observation period.

9. Fecal hardness based on the Bristol stool form scale

Summary statistics of fecal hardness at each week of the treatment period will be calculated and compared with the second week of the observation period by the Wilcoxon signed rank test for the fourth week of the treatment period.

(2) Comparison of the fourth week of the treatment period with the second week of the observation period

1. Constipation Score (CSS)

Summary statistics will be calculated for the total constipation score and compared using the Wilcoxon signed rank test. Summary statistics are also calculated for each symptom and compared by Wilcoxon signed rank test.

2. JPAC-QOL score

Corresponding t-test for change in JPAC-QOL score.

3. Comparison of absolute values and percent composition of bile acid concentrations in feces

Corresponding t-test is performed for the change in bile acid concentration.

(3) Time from taking elobixibat to defecation in each week of the treatment period.

Summary statistics were calculated for the time from elobixibat administration to the first bowel movement in 7 days (median of 7 days) at each week of the treatment period, and the trends were examined.

(4) Examining the relationship between the evaluation items

To examine the relationship between the endpoints such as improvement of loss of defecation desire, patient satisfaction, and bile acid concentration.

16.3.3 Safety Analysis

The number and percentage of cases of SAS will be calculated by disease event and severity.

Vital signs and clinical laboratory values are summarized at each observation time point, and changes over time are shown in graphs.

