## 9.3 Safety evaluation items

　　Incidence rate of diseases, etc.

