# **12. Handling diseases, etc.**

## 12.1 Definition of diseases, etc.

An adverse event is any unfavorable or unintended injury or illness or sign thereof (including abnormal laboratory values) occurring in a subject, whether or not causally related. It includes any exacerbation of a pre-existing disease (not including the primary disease) during the study period.

Among adverse events, in addition to illness, disability, death, or infection, "diseases, etc." refers to abnormalities in clinical laboratory values or symptoms that are suspected to be caused by the conduct of the clinical research. Diseases, etc. attributable to the conduct of clinical research are those that have a causal relationship with the drugs used in the research or with the research procedures. The causal relationship shall be determined by the principal investigator, sub-investigator, or principal investigator based on "12.3 Causal relationship with research.

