## 12.2 Evaluation of diseases, etc.

In this study, the degree (severity) of diseases, etc. occurring from the time of enrollment to the end of taking the study drug will be evaluated as follows.

1) Mild: Can be continued with no treatment

2) Moderate: administration can be continued with some treatment

3) Severe: Conditions for which administration should be discontinued or stopped, etc.

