## 12.3. Causal relationship with research

Causality will be assessed according to the following criteria.

**Causal relationship present or undeniable** - judgment is made according to the following criteria regardless of whether the event in question is known or unknown to occur by the study or intervention treatment.

- - Reasonable or reasonably likely to be attributable to the research or interventional treatment
  - There is a temporal relationship with the study
  - No other cause can be shown, and a causal relationship with the study cannot be ruled out.

**No causal relationship** - to be determined according to the following criteria

- - not reasonably attributable to the research or interventional treatment.
  - temporal relationship cannot be shown
  - Other causes can be shown

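### As defined, the safety endpoint covers only events suspected to be caused by the research, so all-cause adverse event incidence would not be reported

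*Protocol*

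**What the plan says.** Section 12.1 of the protocol uses two terms. An adverse event is any unfavourable occurrence "occurring in a subject, whether or not causally related". The second term, *diseases, etc.*, is introduced as something among the adverse events, and the defining clause says that it "refers to abnormalities in clinical laboratory values or symptoms that are suspected to be caused by the conduct of the clinical research". The section then adds: "Diseases, etc. attributable to the conduct of clinical research are those that have a causal relationship with the drugs used in the research"; a link to study procedures also counts. On who decides, it says: "The causal relationship shall be determined by the principal investigator, sub-investigator, or principal investigator".

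The safety endpoint in section 9.3, repeated in the overview, is "Incidence rate of diseases, etc". The safety analysis in section 16.3.3 reads: "The number and percentage of cases of SAS will be calculated by disease event and severity". The same section also summarises vital signs and laboratory values by time point, with no causal condition.

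Sections 7.2.2 and 7.2.3 list an investigation of adverse events before dosing and at week 4 or end of treatment. Section 17.3 lists *diseases, etc.* and adverse reactions/adverse events as separate central monitoring items. Under sections 6.1 and 15 the trial is open-label and single-arm and has no efficacy and safety evaluation committee.

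**The concern.** The wider category is collected, but the narrower one is the endpoint and the only planned event table. What separates the two is a causality judgement made by someone who knows that every subject takes elobixibat.

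In a controlled trial, a tendency to over- or under-attribute would at least show in both arms. Here there is no comparator and no independent review of causality. An incidence that includes every event does not depend on attribution, and a reader can set it beside other sources. An incidence restricted to suspected events differs between investigators according to how readily each suspects the drug, and the reader cannot undo that if the unrelated events are never tabulated.

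At stake is the completeness and interpretability of the trial's only safety endpoint. The primary efficacy analysis is not affected.

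**Working it through.** The protocol states no figure on this point, so there is none to reproduce. The check compares definitions.

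**Step 1. What the endpoint contains.**

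| Section | Term used | Causal condition |
|---|---|---|
| 12.1, first paragraph | adverse event | none |
| 12.1, second paragraph | *diseases, etc.* | suspected to be caused by the research |
| 7.2.2, 7.2.3 | adverse events (collected) | none |
| 9.3 and overview | *diseases, etc.* (endpoint) | inherited from 12.1 |
| 16.3.3 | disease event (tabulated) | inherited from 12.1 if the defined term is meant |
| 17.3 | both terms, as separate items | shows that they are distinguished |

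No row gives an analysis of adverse events without a causal condition.

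**Step 2. Direction.** Let N be the size of the safety analysis set, A the number of subjects with at least one adverse event after the first dose, and R the number with at least one such event suspected to be caused by the research. Every subject in R is also in A, so R/N ≤ A/N. The difference, (A − R)/N, is the share of subjects whose adverse events were all judged unrelated. A subject with one related and one unrelated event is in both counts and adds nothing to the overall gap, although the unrelated event still drops out of its own row in the table.

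**Step 3. Size.** (A − R)/N needs a rate of unrelated events, or an all-cause rate to set against a related rate. The protocol gives neither. The direction is fixed by the definitions; the size is unknown.

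**Step 4. Is the term used consistently?** It is not.
- Section 12.3, which sits within the chapter on *diseases, etc.*, has a no-relationship category for events "not reasonably attributable to the research or interventional treatment". Under the 12.1 definition that category would be empty.
- Section 12.6.2 asks for causality with the study as well as with the study drug for each disease. The drug field can vary under the narrow definition, but the study field would have only one value.
- Section 12.6.4 attaches the suspected-cause condition to the term again, which would be unnecessary if the term already carried it.

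On the narrow reading, all-cause incidence is not reported. On the broad reading, the endpoint departs from its own definition. Sections 9.3 and 16.3.3 do not say which applies.

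**Step 5. Is the detail collected for unrelated events?** Severity grading in 12.2 and the items in 12.6.2 are specified for *diseases, etc.*. On the narrow reading, nothing requires them for an adverse event judged unrelated. An all-cause table by severity therefore needs that requirement stated.

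**The case against.** The strongest reply is that the causal filter comes from an awkward translation. The defining sentence in 12.1 first mentions illness, disability, death and infection, and the suspected-cause clause may qualify only the laboratory abnormalities and symptoms that follow. The next sentence defines a research-attributable kind of *diseases, etc.*, which suggests that the unqualified term is wider. The inconsistencies in step 4 point the same way. This stands as a reason for caution about intent. It does not remove the point: even if the clause reaches only symptoms and laboratory findings, symptoms remain filtered, and a term with two meanings should not define an endpoint.

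A second reply is that the statistical analysis plan, which is not shown, may add an all-cause table. It may. But 9.3 fixes the endpoint in the protocol, and 16.3.3, unlike 16.3.2, does not defer details to that plan.

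Third, laboratory values and vital signs are summarised whatever their cause, and events before the first dose do not belong in an on-treatment table. Both are correct and limit the omission to clinical event incidence after dosing. The adverse event definition also leaves out worsening of the primary disease, so an all-cause table would not recover symptoms recorded as such.

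A reader might go further in three ways that the protocol does not support:
- That gastrointestinal events are the easiest to call unrelated. Sections 12.3 and 12.4 count an event as related when causality cannot be ruled out, and 12.5 lists abdominal pain, distension and nausea as anticipated reactions. These rules push such events towards related.
- That the 292 of 631 (46.3%) quoted in 12.5 measures the shortfall. It is a rate of adverse reactions, the kind of event that the endpoint would count.
- That the severity table only repeats the action taken on dosing, because of "Severe: Conditions for which administration should be discontinued or stopped, etc". Section 12.2 also grades by need for treatment, and 13.2 records the date of and reason for discontinuation separately.

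**Conclusion.** The point holds in limited form. As written, the only safety endpoint and the only event table rest on a term that 12.1 restricts to events suspected to be caused by the research. All-cause adverse event incidence is therefore not planned, and the safety result depends on unblinded investigator attribution. This assumes that 9.3 and 16.3.3 use the term as 12.1 defines it; looser use in 12.3, 12.6.2 and 12.6.4 leaves that open, and the ambiguity itself needs correcting.

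A reader might infer that the safety results will be understated. That goes too far: the incidence of suspected-related events is not understated by its own definition. The related count can only equal or fall below the all-cause count, and the protocol gives no basis for the size of the difference.

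**What to change.** In sections 9.3 and 16.3.3, and in the matching overview entry, define the safety endpoint as the incidence of all adverse events occurring after the first dose in the safety analysis set, by event and severity. Show events suspected to be related to the research, and those suspected to be related to the study drug, as subsets.

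Reword 12.1 so that *diseases, etc.* has one meaning, and use it consistently in 12.3, 12.6.2 and 12.6.4. State in 12.2 and 12.6.2 that severity and the listed event details are recorded for every adverse event, whatever the causality judgement.

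The cost is one extra table and the recording of those details for unrelated events. No visit is added, and sample size, power and the efficacy analyses do not change.
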